### Interim analyses {21b}

No interim analyses are planned for this trial. The full dataset will be analyzed only after completion of data collection for all participants. This decision was made due to the feasibility-focused design and the relatively small sample size, which would not justify interim statistical testing.

### Methods for additional analyses (e.g., subgroup analyses) {20b}

No predefined subgroup or additional exploratory analyses are planned at this stage.

Given the feasibility nature of this trial and the limited sample size, the study is not powered to detect differences across subgroups. Any future subgroup analysis will require confirmation in larger, follow-up trials.

### Methods in analysis to handle protocol non-adherence and any statistical methods to handle missing data {20c}

Multiple imputation will be used to take into account missing values, provided data is missing at random. If there is a considerable amount of missing data due to protocol violations or discontinuation, application of joint models will be considered to adequately take this information into account.

Data from patients who withdraw their consent to participate during the intervention period of the study will remain in the analysis. If the patients consent to participate in the follow-ups, they will be analyzed as “intent-to-treat” within their original treatment group allocated by randomization.

Based on our experiences with the SepsisDataNet.NRW cohort (a large multicenter study on sepsis patients), we expect a loss to follow-up (30-day survival) of about 10%. Based on our experience from the health-related quality of life study in ECMO patients (see unpublished data above), we expect a follow-up rate of 75% from patients still alive at the time-point of 6-month follow-up. Due to the expected heterogeneity of the study population, no estimation of mortality in the study group can be done at this point.

### Plans to give access to the full protocol, participant-leveldata and statistical code {31c}

All information about the study design and the collected, anonymized data of the study that are not used in the final publication can be provided upon request to the authors.

## Oversight and monitoring

### Composition of the coordinating center and trial steering committee {5d}

This is a single-center, investigator-initiated trial without a formal trial steering committee or coordinating center.

The trial is managed and overseen by the principal investigators (Dr. med. [name] and PD Dr. med. [name]), who are responsible for overall study coordination, protocol adherence, safety oversight, and communication with the ethics committee.

The day-to-day conduct of the trial, including patient recruitment, intervention delivery, and data collection, is managed by the research team from the Departments of Anesthesiology and Intensive Care Medicine and Orthopedics and Trauma Surgery at University Hospital Bonn.

Weekly internal meetings are held to monitor study progress, discuss any issues, and ensure compliance with study procedures and timelines.

### Composition of the data monitoring committee, its role and reporting structure {21a}

For this clinical study, monitoring is not being conducted due to its primary focus on evaluating the design, interventions, and methodology in a limited scope, providing a foundation for a future, larger multicenter trial. The procedures and interventions conducted in this study are safe, well-established, routinely used in comparable studies and following standardized protocols that minimize the risk of deviations. The research team has extensive experience in conducting clinical studies and is well-trained and familiar with the study’s interventions and safety measures. Additionally, the collection and management of study data comply with applicable data protection regulations. Data will be stored pseudonymously, analyzed anonymously, and securely maintained. Lastly, the study was approved by the clinical ethics committee of the University Hospital Bonn as outside the CTR and MDR guidelines, ensuring strict compliance with all ethical guidelines without the need for additional monitoring.

### Adverse event reporting and harms {22}

#### Adverse events and serious adverse events grading

## Adverse event grading

Adverse events will be graded using standard criteria. Relationship of event to the study procedure will be determined by the study physician.GRADE 1 (Mild) Transient or mild discomfort (< 48 h); no medical intervention/therapy requiredGRADE 2 (Moderate) Mild to moderate limitation in activity—some assistance may be needed; no or minimal medical intervention/therapy requiredGRADE 3 (Severe) Marked limitation in activity, some assistance usually required; medical intervention/therapy required, hospitalizations possibleGRADE 4 (Life-threatening) Extreme limitation in activity, significant assistance required; significant medical intervention/therapy required, hospitalization or hospice care probable.

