**Methods:**

This prospective, randomized controlled trial will recruit 120 patients from the surgical ICU at the University Hospital Bonn, who meet the inclusion criteria of a > 48-h ICU stay. Patients will be randomized into four groups: Sham-Control, BFR/IPC, EStim, and combined BFR/IPC + EStim. The study’s primary endpoints include feasibility and safety metrics, such as patient compliance and stress response, alongside secondary endpoints related to clinical outcomes like ICU length of stay, ICUAW prevalence, muscle mass preservation, and rehabilitation efficacy. Measurements include non-invasive assessments of muscle mass, intramuscular microdialysis to monitor metabolic and inflammatory markers, and health-related quality of life evaluations post-discharge.

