### Objectives {7}

ICUAW is a prevalent and severe complication in ICU patients, leading to significant muscle loss, prolonged hospital stays, and increased mortality. Despite the recommendation for early mobilization, existing interventions often fail to prevent or mitigate ICUAW due to practical constraints and insufficient intensity. This feasibility study aims to explore passive physiotherapeutic interventions—blood flow restriction/ischemic preconditioning (BFR/IPC) training, and electromyostimulation (EStim)—as alternative approaches which can be applied to all ICU patients, including those who are sedated or intubated. These techniques could circumvent the challenges of active physiotherapy and address muscle atrophy without exacerbating the patient’s condition or requiring extensive resources. By evaluating the safety, practicality, and effectiveness of these methods, the study seeks to address critical gaps in current ICU rehabilitation practices, potentially improving patient outcomes and reducing healthcare costs.

The present project aims to investigate these two questions by examining the effect of a purely metabolic (blood flow restriction/ischemic preconditioning (BFR/IPC) training), mechanical (electromyostimulation, EStim) or combined metabolic/mechanical load (BFR/IPC + EStim) on the physiology of the critically ill patient and clinical outcome (e.g., ICU length of stay, duration of hospitalization, prevalence of ICUAW, rehabilitation).

For this project, endpoints were defined that primarily reflect the clinical feasibility and safety of the intervention methods and their combinability with the clinical objective of muscle maintenance during ICU therapy and hospitalization. The following domains of outcomes include the evaluation of the impact of the interventions on the clinical rehabilitation process and the description of the underlying mechanisms of possible positive or negative effects on skeletal muscle physiology using invasive diagnostic monitoring.

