### Eligibility criteria {10}

Patients will be recruited on the ICU of the University Hospital Bonn. The patient inclusion criteria are as follows: (1) The study includes all patients under intensive care monitoring and therapy with a length of stay > 48 h in the surgical intensive care units of the University Hospital Bonn. (2) All participating patients have signed the patient consent form for study participation as well as the privacy policy after comprehensive explanation, explanation and information or have been represented by the spouse as part of the spouse’s emergency representation after comprehensive explanation. (3) Patients aged > 18 years are included. Exclusion criteria for the study are: (1) acute or chronic infections of the extremities, (2) open wounds on the lower extremity, (3) Pregnancy and breastfeeding, (4) sickle cell anemia, and (5) former surgical interventions on the thigh vessels (e.g., stenting, bypassing).

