#### Adverse event reporting procedures

Reporting responsibilities:*○ Participants*: Report any unusual or unexpected symptoms or experiences to study staff immediately by phone or by mobile app*○ Study staff*: Document all reported events promptly and ensure proper communication with the principal investigator (PI).Identification and classification:*○ Type of Event*: Describe the nature of the event (e.g., physical injury, psychological distress).*○ Severity*: Grade the severity from Grade 1 to Grade 4.*○ Causality assessment*: Determine whether the AE is related to the study intervention (unrelated, unlikely-, possibly-, probably-, or definitely related).Documentation:○ Record the AE in the *Adverse Event Log* or study-specific Case Report Form.○ Include the following details:Date and time of onset.Date and time of onset.Severity and duration.Actions taken (e.g., treatment provided, intervention discontinued).Outcome (resolved, ongoing, worsened).Immediate reporting of serious adverse events:Any serious adverse event (e.g., life-threatening reaction, hospitalization) must be reported to the ethics committee and study sponsor within 24 h. Include:○ Detailed description of the event.○ Detailed description of the event.Follow-up:○ Monitor the participant until the AE resolves or stabilizes.○ Update the AE report with follow-up information.Regulatory reporting:○ Submit regular AE summaries to the ethics committee per protocol requirements.○ Ensure timely reporting of unexpected or related SAEs to relevant authorities.Preventive actions:○ Review AEs regularly to identify trends or risk factors.○ Update the study protocol, participant materials, or safety measures if needed.

Given the nature of the interventions (blood flow restriction, electrical stimulation), potential expected adverse events include:Local skin irritation or redness at electrode or cuff sitesTransient muscle discomfort or sorenessMild circulatory changes (e.g., temporary blood pressure fluctuations)

*All participants will be systematically monitored* for adverse events throughout the study, including vital signs before, during, and after each intervention. Clinical staff will record any observed events, and participants (or their representatives) will be asked about symptoms using *open-ended questions* as well as *standardized observation forms*.

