Any *unexpected harms* will also be documented and reviewed by the principal investigators. All adverse events will be graded based on severity and relatedness to the study intervention using the predefined grading scale in the protocol (Grades 1–4).

While we do not use MedDRA coding, all events will be categorized using standardized medical terminology in accordance with ICH-GCP and institutional reporting standards.

*All adverse events of Grade 2 or higher*, or those classified as serious (SAEs), will be reported in trial publications. Grade 1 (mild) events will be summarized descriptively unless they are unusually frequent or clustered.

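### The adverse-event severity scale has no fatal grade or outcome, and its activity and hospitalisation anchors are largely met already by ICU inpatients, so the Grade 1/2 boundary is poorly defined

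*Protocol article*

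**What the plan says.** Under Adverse event reporting and harms {22}, the protocol article prints a four-grade severity scale. Grade 4, labelled life-threatening, is described as "Extreme limitation in activity, significant assistance required; significant medical intervention/therapy required, hospitalization or hospice care probable". The reporting procedures tell staff to "Grade the severity from Grade 1 to Grade 4", and the closing paragraphs of the section repeat that all events are graded "using the predefined grading scale in the protocol (Grades 1–4").

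The event record must also carry an outcome, with these options: "Outcome (resolved, ongoing, worsened"). For rapid reporting the text says "Any serious adverse event (e.g., life-threatening reaction, hospitalization) must be reported" to the ethics committee and sponsor within 24 h.

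Trial publications are to report events of Grade 2 or higher and all serious events. Grade 1 events are only summarised descriptively, unless they are unusually frequent or clustered.

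Eligibility criteria {10} require a "length of stay > 48 h in the surgical intensive care units". Objectives {7} extend the interventions to all ICU patients, "including those who are sedated or intubated".

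**The concern.** A severity scale has to measure the event, not the state the patient was in beforehand. Limits on activity, need for help and likelihood of hospital admission are natural anchors for people living at home. In an ICU they mostly describe the starting point. The scale also stops short of death, in a population where the protocol itself makes hospital and 28-day mortality endpoints.

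The abstract states that the "primary endpoints include feasibility and safety metrics", and the stated hypothesis compares the arms on safety. There is no data monitoring committee and no formal audit. The investigators' own review of the event records is therefore the main way a pattern of harm would be noticed. If two assessors can give the same event different grades, the published harms table loses meaning, and so does any informal look for trends.

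**Working it through.** No arithmetic applies: no rate, sample size or power figure enters the point. The check sets the scale against the population, one anchor at a time.

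| Grade | Activity and assistance | Hospitalisation | Treatment | Other |
|---|---|---|---|---|
| 1 | not mentioned | not mentioned | none | transient or mild discomfort, under 48 h |
| 2 | mild to moderate limit; help may be needed | not mentioned | none or minimal | – |
| 3 | marked limit; some help usual | possible | required | – |
| 4 | extreme limit; substantial help | probable (or hospice) | significant | labelled life-threatening |

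**Step 1: hospitalisation.** Every participant has been in a surgical ICU for more than 48 h (Eligibility criteria {10}). The anchor is met by all of them at entry and stays uninformative until discharge.

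**Step 2: activity and assistance.** For sedated or intubated patients, whom Objectives {7} expressly includes, severe limitation is certain before any event. For conscious ICU patients it is a reasonable inference, not something the protocol states.

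**Step 3: treatment.** This anchor appears in all four grades and still discriminates. However, the objectives and the outcomes section show that patients may already be on circulatory support, analgesics and sedatives. The scale does not say that the treatment counted is treatment added because of the event.

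**Step 4: the Grade 1/2 boundary.** Grade 1 means no treatment. Grade 2 means none or minimal, so the treatment anchor does not separate the two when nothing is given. What remains is activity limitation (Step 2), discomfort, which a sedated patient cannot report, and the 48 h limit.

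The protocol's own expected events make suitable test cases:

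- Brief skin redness under a cuff in a sedated patient, untreated. Grade 1 fits by duration and absence of treatment. Grade 2 fits if the patient's limited activity is counted. Grades 3 and 4 do not fit, because no treatment was needed.
- A temporary fall in blood pressure in a patient already receiving noradrenaline, with the existing infusion adjusted. Nothing in the scale says whether that adjustment counts as none, minimal, required or significant treatment.

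In the first case the choice of grade decides whether the event crosses the publication threshold. In the second it may do so.

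**Step 5: a fatal event.** All events must receive a grade from 1 to 4 and one of the three listed outcomes. A fatal event must be merged with survivable life-threatening events in Grade 4 or left ungraded. None of the three outcomes says that the patient died.

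**Step 6: serious-event examples.** During the inpatient intervention week a new admission cannot occur. Death and prolonged stay, the outcomes more relevant at that stage, are not among the two examples given. After discharge, admission becomes a new and informative event, because follow-up runs to 12 months and readmission is an endpoint.

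**The case against.** The strongest reply is that this is a matter of coding and not of endpoints, and much of that stands. Four stronger readings are tempting, and the documents do not support them.

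- *That the primary safety endpoint itself is broken.* A reader might infer this from the abstract. The objectives, however, define safety through circulatory, analgesic and sedative drug use, respiratory gases, and inflammation and coagulation values. Grade is not part of that definition, and the statistical section plans no between-arm test of grades.
- *That mild events cannot be told from severe ones.* They can, in large part. The treatment anchor and the 48 h limit still separate Grade 1 from Grades 3 and 4, and a harmless untreated event in a sedated patient does not become Grade 3.
- *That the 24 h reporting duty depends on the grades.* It is triggered by seriousness. Serious events are also published whatever their grade, and deaths are recorded as hospital and 28-day mortality, so they are not lost to the trial.
- *That the expected loss of about 10% by 30 days gives a count of ungradable deaths.* The protocol declines to estimate mortality in this population, so no such count can be derived.

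It can also be said that the serious-event wording is a list of examples in a journal article and that a full definition may exist elsewhere. That is fair: the absence of death from two examples would not be a finding on its own.

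The reply does not reach the scale. The scale is printed in full, described as the predefined one, and staff are told to use its four grades. A fuller document would have to contradict it in order to repair it.

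**Conclusion.** The point holds as a defect in how harms are classified. A fatal event has neither a grade nor an outcome category. The hospitalisation anchor is uninformative for every participant while in hospital. The activity anchor is uninformative for the sedated and probably weak for the others. Severity then rests almost wholly on a treatment anchor that is not tied to additional treatment, and the Grade 1/2 boundary, which sets the publication rule, is close to unusable as written.

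The size is qualitative. No planned test, listed primary endpoint or mortality count changes. What is affected is the comparability of grades between assessors and the content of the published harms report. The conclusion assumes that the printed scale is the one to be used, as the text says. It also assumes that conscious ICU patients are materially limited in activity, which is inferred. The change is worth making because safety is a stated primary aim, independent oversight is absent and the trial is listed as in preparation.

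**What to change.** 1. Anchor Grades 1 to 4 on the additional intervention needed because of the event and on change from the patient's status immediately before it, in place of activity limitation and hospitalisation.
2. Add Grade 5 for death, and change both statements of the grade range to 1 to 5.
3. Add a fatal category to the list of event outcomes.
4. Add death and prolongation of ICU or hospital stay to the serious-event examples. Keep new hospitalisation there, so that readmission during follow-up remains a named example.
5. Keep the relatedness categories and the rule that events of Grade 2 or higher are published, applied to the revised scale.

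The cost is a revised adverse-event form, brief training of staff on the new anchors and an ethics submission, all before recruitment. Sample size and planned analyses are unaffected.

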### Relationship assignment

The relationship of the adverse event to participation in the study will be assessed as either:Definitely related Probably relatedPossibly relatedUnlikely relatedUnrelated

#### Adverse event reporting procedures

Reporting responsibilities:*○ Participants*: Report any unusual or unexpected symptoms or experiences to study staff immediately by phone or by mobile app*○ Study staff*: Document all reported events promptly and ensure proper communication with the principal investigator (PI).Identification and classification:*○ Type of Event*: Describe the nature of the event (e.g., physical injury, psychological distress).*○ Severity*: Grade the severity from Grade 1 to Grade 4.*○ Causality assessment*: Determine whether the AE is related to the study intervention (unrelated, unlikely-, possibly-, probably-, or definitely related).Documentation:○ Record the AE in the *Adverse Event Log* or study-specific Case Report Form.○ Include the following details:Date and time of onset.Date and time of onset.Severity and duration.Actions taken (e.g., treatment provided, intervention discontinued).Outcome (resolved, ongoing, worsened).Immediate reporting of serious adverse events:Any serious adverse event (e.g., life-threatening reaction, hospitalization) must be reported to the ethics committee and study sponsor within 24 h. Include:○ Detailed description of the event.○ Detailed description of the event.Follow-up:○ Monitor the participant until the AE resolves or stabilizes.○ Update the AE report with follow-up information.Regulatory reporting:○ Submit regular AE summaries to the ethics committee per protocol requirements.○ Ensure timely reporting of unexpected or related SAEs to relevant authorities.Preventive actions:○ Review AEs regularly to identify trends or risk factors.○ Update the study protocol, participant materials, or safety measures if needed.

Given the nature of the interventions (blood flow restriction, electrical stimulation), potential expected adverse events include:Local skin irritation or redness at electrode or cuff sitesTransient muscle discomfort or sorenessMild circulatory changes (e.g., temporary blood pressure fluctuations)

*All participants will be systematically monitored* for adverse events throughout the study, including vital signs before, during, and after each intervention. Clinical staff will record any observed events, and participants (or their representatives) will be asked about symptoms using *open-ended questions* as well as *standardized observation forms*.

Any *unexpected harms* will also be documented and reviewed by the principal investigators. All adverse events will be graded based on severity and relatedness to the study intervention using the predefined grading scale in the protocol (Grades 1–4).

While we do not use MedDRA coding, all events will be categorized using standardized medical terminology in accordance with ICH-GCP and institutional reporting standards.

*All adverse events of Grade 2 or higher*, or those classified as serious (SAEs), will be reported in trial publications. Grade 1 (mild) events will be summarized descriptively unless they are unusually frequent or clustered.

